##### Image analysis

3.4.1.1

Images will be reviewed by 2 nuclear medicine specialists at the Department of Nuclear Medicine at Odense University Hospital who are blinded to clinical and laboratory data. FDG uptake patterns will be recorded in a descriptive manner with regard to nonarterial uptake and recorded in 6 arterial compartments for each individual patient including thoracic and abdominal aorta, carotid, subclavian, femoral, and iliac arteries. A visual 4-point scale, as described by earlier studies,^[7,27–29]^ will be used for every arterial segment as follows:0: No uptake1: Slight uptake but not negligible, lower than liver uptake2: Intermediate uptake, similar to liver uptake3: High-grade intense uptake, higher than liver uptake

A score of ≥2 and <2 will be considered PET-positive and PET-negative, respectively. SUVs will be measured for quantitative analysis for each arterial segment and calculated as follows: 

Global disease burden will be expressed as follows:

cMVP = ∑ (MAV∗cSUVmean), where

cMVP = partial volume corrected metabolic volume product,

MAV = metabolic active volumes, and

cSUVmean = partial volume corrected mean standard uptake value

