## Introduction

1

Polymyalgia rheumatica (PMR) is the most common inflammatory rheumatic disease that affects individuals over the age of 50 years. The typical symptoms of PMR are bilateral aching and stiffness in selected muscle groups, predominantly in the neck, shoulders, upper arms, and pelvic girdle that are most pronounced in the morning and improve with physical activity.^[1–3]^ Giant cell arteritis (GCA) is an inflammatory vasculopathy that typically involves medium and large arteries.^[4]^ Though involvement of the extracranial branches of the carotid artery can be identified in the classic cranial GCA, GCA may also involve aorta and its major branches, predominantly branches of the proximal aorta, that is, subclavian, axillary proximal brachial arteries, representing a subset of patients with large-vessel GCA (LV-GCA).^[4,5]^ Vasculitis, if untreated, can result in ischemic complications, such as ischemic optic neuropathy, which is responsible for vision loss in 10% to 15% of patients. Whereas the etiology of PMR/GCA is still unknown, genetic and environmental factors may play roles in the development of PMR/GCA. GCA and PMR share many pathogenetic and epidemiological features, and are frequently thought to represent different spectrums of the same clinical entity. Despite the high association between PMR and GCA, it is essential to differentiate these 2 conditions due to different steroid treatment regimes. Corticosteroids are considered the treatment of choice for PMR/GCA, with higher doses required for GCA.^[1–3]^ PMR/GCA is generally not associated with reduced longevity; however, patients with aortic aneurysm/dissection have higher rates of mortality.^[6]^ Additionally, patients are at risk of different comorbidities, both due to the disease characteristic itself and also due to treatment side effects.

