### Study setting

3.1

The current study will be performed at the Department of Rheumatology, Svendborg Hospital, Odense University Hospital, Svendborg, Denmark. The Rheumatology Department of Svendborg Hospital has the capacity of enrolling PMR/GCA patients that are required for this study, since all patients from all over Funen County with suspicious PMR/GCA will be referred to the Diagnostic Center for primary investigation at Svendborg Hospital. After confirmed PMR/GCA condition the patients will be referred to the local Rheumatology department for study inclusion.

All parts of the project will take place at Svendborg Hospital, except the 18F-FDG PET/CT scans and bone densitometry, which will be undertaken at the Department of Nuclear Medicine and Department of Endocrinology, respectively, Odense University Hospital, Odense, Denmark. The 18F-FDG PET/CT will be performed as routine whole-body scan (from vertex of the skull to the knees) 60 minutes after injection of a weight-adjusted dose of FDG according to the guidelines from the European Association of Nuclear Medicine.^[25]^ The CT-part is a low-dose CT without contrast enhancement.

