### Participants

3.3

All new patients with clinical suspicion of PMR/GCA will be offered to be included in the study. At least 5 (A–E) components of the PMR diagnostic criteria, including: age ≥50 years, bilateral shoulder or hip pain, morning stiffness lasting >45 minutes, elevated ESR, elevated CRP, disease duration >2 weeks, should be met to suspect PMR.^[3]^ For GCA, the following criteria must be considered: age >50 years, ESR/CRP >50, and also at least 2 symptoms related to vasculitis (scalp tenderness, vision disturbances, headache [new or changed], jaw claudication, tenderness of the temporal arteria) if patients do not simultaneously have PMR. If the patient is suspected for PMR, 1 cranial symptom is enough to suspect GCA. Besides, clinical suspicion of LV-GCA, that is, upper-extremity claudication, upper-extremity blood pressure discrepancies, and abnormal radial pulse, will be registered.

The exclusion criteria (study I–IV) are as follows:1.Patients with dementia or inability to communicate in Danish2.Infections or malignancy when prednisolone is permanently unsuitable3.Contraindication to imaging studies (pregnancy and blood sugar [BS] >8 mmol/L after 6 hours fasting)4.Initiation of steroid treatment before the 18F-FDG PET/CT scan5.Inability to provide informed consent

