After 1 year, the 18F-FDG PET/CT results will be unveiled and these parameters will be compared in the succeeding groups of patients: patients with vasculitis in the large vessels (PET-positive); patients without vasculitis in the large vessels (PET-negative); patients with findings compatible with PMR (PET-positive); and patients with vasculitis in the large vessels together with findings compatible with PMR (PET-positive). The classification of 18F-FDG PET/CT results (PET +/−) is based on visual assessment in a descriptive manner, and also quantitative methods. The visual assessment is based on simple visual assessment of FDG uptake patterns in a descriptive manner (PMR) and a 4-point scale of FDG uptake in the vessels (GCA). The visual assessment will be compared with simple semiquantitative analyses, that is, so-called maximum standard uptake value (SUVmax), a simple delineation of the single voxels with the highest tracer uptake. This is a simple procedure available with the generic software indigenous to the scanners and provided by the vendors, for example, in our case, GE Advantage Server 2.0 (GE Healthcare, Milwaukee, WI). It is easily applicable in clinic, but highly variable and prone to both technical and patient related pitfalls. Thus, a third method of quantification will be employed and compared with the visual assessment and SUVmax, that is, global disease burden,^[31]^ which is based on more elaborate, and therefore technically cumbersome, computations involving segmentation, quantification, and summing of all FDG-avid lesions with pathologic activity defined by predetermined threshold. These metabolically active volumes (MAVs) will be summed to yield a global disease score, a metabolic volume product (MVP) of all PET-positive lesions throughout the body. This seems to be a very robust method, but also somewhat cumbersome to implement in daily clinical practice.

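### The six scored arterial compartments leave out the axillary and proximal brachial arteries, so uptake confined to those vessels is classed as no large-vessel vasculitis

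*Protocol article*

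**What the plan says.** Section 3.4.1.1 (Image analysis) of the protocol article has arterial uptake "recorded in 6 arterial compartments for each individual patient including thoracic and abdominal aorta, carotid, subclavian, femoral, and iliac arteries". Each segment is scored from 0 to 3 against liver uptake, and "A score of ≥2 and <2 will be considered PET-positive and PET-negative, respectively". SUV is measured for the same segments. For uptake outside the arteries, "FDG uptake patterns will be recorded in a descriptive manner with regard to nonarterial uptake".

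Section 3.4.1 (Study I) says that PET status "is based on visual assessment in a descriptive manner, and also quantitative methods". For GCA the visual element is "a 4-point scale of FDG uptake in the vessels (GCA" in that section's wording. The section forms four groups: large-vessel vasculitis, no large-vessel vasculitis, PMR-compatible findings, and both together.

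The Introduction says that extracranial GCA can affect the aorta as well as the vessels arising from it, and specifies the latter as "predominantly branches of the proximal aorta, that is, subclavian, axillary proximal brachial arteries, representing a subset of patients with large-vessel GCA (LV-GCA". Section 3.3 (Participants) adds that "clinical suspicion of LV-GCA, that is, upper-extremity claudication, upper-extremity blood pressure discrepancies, and abnormal radial pulse, will be registered". Section 3.1 describes the acquisition as a "routine whole-body scan (from vertex of the skull to the knees".

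**The concern.** The list of scored vessels does not match the protocol's own account of where large-vessel GCA sits. Of the three branch sites that the Introduction names as predominant, only the subclavian is scored. The iliac and femoral arteries, which the Introduction does not name, are scored. The signs registered for large-vessel GCA are all upper-limb signs, the territory that the axillary and brachial arteries supply. The article gives no reason for the omission.

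PET status defines the groups in the primary Study I comparison and is one side of the biopsy agreement in Study II. A patient placed in the wrong vasculitis group therefore carries the error into both analyses.

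**Working it through.** The article states no figure to reproduce here. The check is a comparison of sections, followed by an illustration of size.

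**1. Is the list closed?** Thoracic aorta, abdominal aorta, carotid, subclavian, femoral, iliac: 1 + 1 + 1 + 1 + 1 + 1 = 6, the number stated. There is no room for a further site.

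**2. Could another stated rule catch the uptake?**
- Descriptive recording covers only nonarterial uptake.
- SUV is taken per scored segment, so it has the same gap.
- Global disease burden sums all PET-positive lesions in the body and could include an axillary lesion, but no cut-off turns it into PET-positive or PET-negative.

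No written rule lets axillary or brachial uptake change PET status.

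**3. Who is affected?** The article does not write out how segment scores combine for a patient. I assume that any scored segment at 2 or more makes the patient positive.

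| Arterial uptake | PMR-compatible uptake | Class under the six-compartment list |
|---|---|---|
| Axillary/brachial plus a scored segment at ≥2 | either | Large-vessel vasculitis (unaffected) |
| Axillary/brachial only | no | PET-negative |
| Axillary/brachial only | yes | PMR findings only, instead of PMR plus vasculitis |

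**4. How many patients?** The article gives no rate of isolated axillary or brachial disease, so both scenarios rest on assumptions.

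*Scenario A.* Section 3.4.4 puts clinically apparent large-vessel disease at 9% to 14% of GCA cases, and Section 3.9 plans 80 patients. Treating all 80 as GCA, which is an upper bound for this step:
- 0.09 × 80 = 7.2 and 0.14 × 80 = 11.2 large-vessel cases.
- With an assumed 5% to 20% isolated: 0.05 × 7.2 = 0.4 and 0.20 × 11.2 = 2.2 patients misclassed.

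*Scenario B.* PET may show more disease than is clinically apparent. With an assumed 20 large-vessel cases on PET and 10% to 30% isolated: 0.10 × 20 = 2 and 0.30 × 20 = 6 patients misclassed.

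**5. What would Scenario B do to Study I?** Take a simple comparison of vasculitis against no vasculitis in 80 patients. Assume that the misplaced patients have the same mean outcome as the scored vasculitis cases. The observed difference is then the true difference × (1 − m/n₀), with m misplaced patients in a comparison group of n₀. The half-width of the 95% CI, in SD units, is t(0.975, 78) × √(1/n₁ + 1/n₀), with t = 1.99.

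| Misplaced | n₁ / n₀ | Contamination m/n₀ | True 0.50 SD becomes | CI half-width |
|---|---|---|---|---|
| 0 | 20 / 60 | 0% | 0.50 SD | 0.51 SD |
| 2 | 18 / 62 | 2/62 = 3% | 0.48 SD | 0.53 SD |
| 6 | 14 / 66 | 6/66 = 9% | 0.45 SD | 0.59 SD |

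**6. What would it do to Study II?** Take a patient with axillary-only uptake who should have been PET-positive and is called PET-negative. If the biopsy is negative, a discordant pair becomes concordant and agreement rises by 1/80 = 1.25 percentage points (assuming that all 80 have both tests). If the biopsy is positive, agreement falls by the same amount. Section 3.8 counts PMR-compatible findings within PET positivity for the agreement on positive results, so a patient with such findings may not change cell there at all.

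**The case against.** The strongest reply is that the chosen segments are reasonable for this study. The Introduction names the aorta as well as its branches, and both aortic segments and the first-named branch are scored. The Discussion (Section 4) expects PET to delineate mainly the thoracic aorta, carotid and subclavian arteries, and all three are on the list. The study is explorative, the disease-burden measure may still register axillary uptake, and a condensed article may leave segment boundaries to a reading manual.

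Much of this limits the size of the problem, but it does not remove the gap. The Discussion's list of what PET mainly shows is not exclusive, and the plan already goes beyond it by scoring the iliac and femoral arteries. The disease-burden measure has no route into PET status. A manual could define where the subclavian segment ends, but the article itself fixes the number of compartments at six.

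A reader might infer four stronger things that the article does not support:
- *Every patient with axillary or brachial disease is classed PET-negative.* Only patients with no scored segment at 2 or more are affected, and those with PMR-compatible uptake are still labelled PET-positive.
- *Agreement with biopsy is lowered.* The direction depends on the biopsy result. The Introduction says that biopsy does not show extracranial disease, so a negative biopsy in such a patient is quite possible, and agreement would then rise.
- *The Study IV comparison with pulse wave velocity is damaged.* Section 3.4.4 compares aortic velocity with PET vasculitis, and both aortic segments are scored.
- *Every group difference shrinks.* That requires misplaced patients to resemble the scored vasculitis cases on each outcome, which nothing in the article establishes.

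**Conclusion.** The point holds in a narrow form and is minor. As written, the visual scale cannot detect vasculitis confined to the axillary or proximal brachial arteries, although the protocol names these among the predominant branch sites and registers signs from the same territory.

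The number misclassed cannot be derived from the article. About 0 to 2 of 80 (Scenario A) and 2 to 6 of 80 (Scenario B) are illustrations, resting on an assumed isolated share and, in B, an assumed 20 PET cases. Neither should be quoted as an expected count. Even under B the shrinkage of 3% to 9% is small beside a confidence interval half-width above 0.5 SD. The tendency in Study I is towards dilution, and the direction in Study II is unknown. The reason to act is that the correction is cheap, not that the effect is large.

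**What to change.** In Section 3.4.1.1, add the axillary and proximal brachial arteries as a seventh compartment. Score it on the same 0 to 3 scale and count it under the existing rule of 2 or more. Allow an entry of not assessable for scans where the segment cannot be judged. The same two blinded readers can score it on the existing scans, and if reading has begun it can be a further blinded read of the stored images. Report the six-compartment classification as a sensitivity analysis, so that any effect of the added segment is visible. If the segment is left out on purpose, state the reason.

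The cost is slightly more reading time per scan and some unscorable segments. No new scan or staff is needed.

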#### Study II: evaluating validity of 18F-FDG PET/CT scan for diagnosis of polymyalgia rheumatica and giant cell arteritis compared to temporal artery biopsy: an agreement study

3.4.2

Recent literature is in favor of the ability of 18F-FDG PET/CT scan to detect vasculitis at an early stage, which is important to decide on treatment plan.^[32]^ However, the superiority of 18F-FDG PET/CT scan in comparison with TAB is still arguable. This study will compare 18F-FDG PET/CT scan to TAB. As mentioned in the study I, all included patients will undergo an 18F-FDG PET/CT scan. In addition to 18F-FDG PET/CT scan, TAB will be performed before or within 1 week of steroid treatment initiation. TAB will be taken by experienced otolaryngologist at Department of Ear, Nose and Throat, Svendborg Hospital. The results of biopsy will be compared with the 18F-FDG PET/CT findings after 1 year, when the 18F-FDG PET/CT results are revealed and compared with regards to the degree of agreement between the 2 modalities.^[33,34]^

##### Temporal artery biopsy procedure

3.4.2.1

In patients with lateralizing symptoms, the biopsy will be taken from the symptomatic side. The superficial temporal artery will be palpated and marked with a surgical marker. The site will be shaved if is necessary. Local anesthetic will be injected into the skin and subcutaneous tissue corresponding to planned incision using lidocaine 1% with or without adrenalin. Under sterile condition the incision will be made at the previously marked skin site. The incision should be large enough to uncover 2 to 3 cm of the vessel. The dissection will be carried through the subcutaneous fat and the artery will be identified just beneath the temporoparietal fascia. The artery will be ligated proximally and distally, and so the intervening segment will be cut out and fixated in formaldehyde. The in vivo specimen should be minimum 1.5 cm in length. At last, skin will be sutured using non-absorbable suture material.

##### Preparation of specimens for pathologic examination

3.4.2.2

The biopsy will be fixed in formalin for 24 hours, divided in sections of 3 to 4 mm, embedded in paraffin, cut in step sections, and stained with Weigert elastin and hematoxylin and eosin (H&E), respectively. Additional sections will be cut for later analysis. Some of the additional sections will include deeper sections in the block to further evaluate the extent of the lesion. The additional analysis will include immunohistochemistry for inflammatory cells, proliferation markers and markers of fibrosis.

#### Study III: prevalence of newly diagnosed malignancies in patients with polymyalgia rheumatica and giant cell arteritis, or polymyalgia rheumatica like syndrome with a focus on 18F-FDG PET/CT compared with CXR/abdominal US: a blinded, prospective, explorative study

3.4.3

The relationship between PMR/GCA and malignancies remains controversial. There are several reports regarding the association of PMR and malignancies. In a database study from Sweden, where 35,918 patients after hospitalization for GCA and PMR were included, there was a marginally increased incidence of cancer in patients with GCA compared with the general population (standardized incidence ratio 1.19, 95% confidence interval [CI] 1.06–1.23). However, when evaluating malignancy risk in the first year after diagnosis of PMR or GCA, the standardized incidence ratio was 2.26 (95% CI 2.10–2.42).^[35]^ Another study utilized the UK General Practice Research Database and evaluated cancer risk in 2877 patients with PMR, without pre-existing cancer or vascular disease and treated with corticosteroids, who were matched with up to 5 age, sex, and general practice patients without PMR. Over a median follow-up of 7.8 years, 23.2% of patients with PMR developed cancer compared with 19.5% of controls. The risk of malignancy was increased in patients with PMR during the first 6 months after diagnosis (hazard ratio [HR] 1.69, 95% CI 1.18–2.42).^[36]^ However, the risk of misclassification/misdiagnosis in database studies is notable, which also points out the need for studies with prospective design. Danish Rheumatology Association recommends the screening for malignant diseases in PMR/GCA patients.^[3]^ Various malignancies can cause PMR-like symptoms; therefore detailed assessment to exclude occult malignancies seems to be rational, especially in patients with atypical manifestations.^[37,38]^ Patients with malignant disease may also present with remitting seronegative symmetrical synovitis with pitting edema, which is a closely related condition to PMR.^[39,40]^

This study is a blinded prospective investigation. At diagnosis all patients undergo a CXR and abdominal US, as recommended by the Danish Rheumatology Association. The 18F-FDG PET/CT scan in every included patient (as described in study I) will be assessed with regards to malignancies before results are blinded to the clinicians for 1 year. This assessment will be blinded to other clinical and imaging results and findings on 18F-FDG PET/CT scan will be compared with CXR/abdominal US results to establish the relative diagnostic accuracy of these 2 strategies for malignant and infectious diseases in PMR/GCA patients. In case of detecting or developing any kinds of malignant disease during the study, the patients will be referred to the relevant department for further work-up and treatment. This will not be a reason for exclusion, but depends on individual assessment of the patient. 18F-FDG PET/CT scan may also be repeated for individual patient if necessary.

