#### Study I: the association of clinical picture of polymyalgia rheumatica and giant cell arteritis with 18F-FDG PET/CT findings: 1-year, prospective, blinded explorative study

3.4.1

The current study is a 1-year prospective, blinded, and explorative study. This is the first study of its kind, to our knowledge, to evaluate the association between the clinical picture of PMR/GCA and 18F-FDG PET/CT findings in a prospective setting. Previous study revealed the correlation between serological markers of inflammation and FDG accumulation in PMR.^[7,26–28]^ However, the small sample size was a major limitation. On the contrary, some reports failed to show this correlation.^[9,29,30]^

All included patients initially will undergo an 18F-FDG PET/CT scan. The results of the 18F-FDG PET/CT scans will not be made accessible to the treating physician in daily clinical routine, but unexpected findings or findings requiring further diagnostic tests or intervention will be relayed to the chief physicians responsible for inclusion. The results of 18F-FDG PET/CT scan will be blinded for both the clinicians and patients. During the year after the initial 18F-FDG PET/CT scan, the following clinical data will be monitored: cumulated prednisolone doses (using patient diaries), well-being of the patients (including visual analog scale [VAS], patient's assessment of pain, morning stiffness [minute], VAS for physicians’ evaluation), ESR, CRP, fibrinogen, and the eventual number of relapses. Definition of remission and relapse is based on expert opinion considering the following parameters: patient's assessment of pain, morning stiffness, ESR, CRP, clinical examination findings (eg, shoulder pain/limitation, upper extremity blood pressure discrepancies, vascular bruits and aortic regurgitation murmur), and steroid dose which is required to control symptoms.

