### Outcomes

3.8

The primary outcome measure are as follows:1.To evaluate the cumulated prednisolone doses, VAS, patients’ assessment of pain, morning stiffness, VAS for physician evaluation, biochemistry results, that is, ESR, CRP, and fibrinogen, and the eventual number of relapses at baseline and during the first year after treatment initiation (weeks 12, 24, 36, and 48) in patients with PET-positive and PET-negative as described above.

The secondary outcome measures are as follows:1.To elucidate the degree of agreement between PET positivity (vasculitis in the large vessels, and also findings compatible with PMR) and TAB positivity.2.To elucidate the degree of agreement between PET negativity (no signs of vasculitis in the large vessels) and TAB negativity.3.To reveal the prevalence of malignancies in the patients detected by the aim of 18F-FDG PET/CT scan and subsequently compare to the prevalence of malignancies detected by the aim of CXR plus abdominal US.4.To reveal the prevalence of malignancies in the patients detected by the aim of CXR plus abdominal US and subsequently compare to the prevalence of malignancies detected by the aim of 18F-FDG PET/CT scan.5.To evaluate BMI, T score, Z score, LBM, FM, BMD, BMC, FFM, FFMI, and FMI at baseline and after 1 year of treatment initiation.6.To evaluate aortic PWV, upper limb PWV, and aortic augmentation index of included patients at baseline and during treatment (weeks 12, 24, 36, and 48).

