### Statistical analysis

3.12

It is anticipated that 80 participants are likely to be included during a period of 1 year. The results will be considered as significant if *P* value <0.05. Statistical analysis has been discussed below with respect to each individual study.

In study I, data will be descriptive (mean ± standard deviation). Comparisons of the data, between the PET-positive and PET-negative patients, will be made with the Mann–Whitney *U* test or Student *t* test, depending on whether or not the distribution is normal. When comparing 2 binary variables, the chi-square test will be performed. Correlation analysis will be performed with Pearson correlation test.

Study II consists of descriptive statistics and proportions of agreement.

Study III consists of descriptive statistics. Comparisons between groups will be made with McNemar test. The sample size of 80 patients is sufficient to indicate a difference of 15% in detection rate of malignancies with 18F-FDG PET-CT scan as opposed to CXR plus abdominal UL (with a significance level of 5% (1-sided), power of 80%, and assuming discordant proportions of 15% and 0%).^[52]^

Study IV consists of descriptive statistics. Univariate comparisons between groups will be made with the Mann–Whitney *U* test or Student *t* test, depending on whether or not the distribution is normal. When comparing 2 binary variables, the chi-square test will be performed. Analysis of repeated measurements over time will be done by means of mixed linear models, using standard errors that allow for intragroup correlation, relaxing the usual requirement that the observations be independent. Comparison of the above mentioned baseline data, matched by age and sex, will be made, to the extent that these data are available.

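### Study III aims at relative diagnostic accuracy, but its only planned comparison, a McNemar test on malignancies detected, can support a statement about yield and not one about accuracy

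*Protocol article*

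**What the plan says.** **Aim.** The abstract says that Study III focuses on the diagnostic accuracy of PET/CT against the conventional work-up. Section 3.4.3 says that "findings on 18F-FDG PET/CT scan will be compared with CXR/abdominal US results" in order "to establish the relative diagnostic accuracy of these 2 strategies for malignant and infectious diseases in PMR/GCA patients".

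**Outcomes.** Section 3.8, secondary outcome 3, reads "To reveal the prevalence of malignancies in the patients detected by the aim of 18F-FDG PET/CT scan", to be set against the prevalence found by chest X-ray plus abdominal ultrasound. Outcome 4 is the same comparison in the other direction. No outcome concerns infection.

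**Analysis.** Section 3.12: "Study III consists of descriptive statistics. Comparisons between groups will be made with McNemar test". The planning statement there is also about detection: "The sample size of 80 patients is sufficient to indicate a difference of 15% in detection rate of malignancies", at one-sided 5% and 80% power, with discordant proportions of 15% and 0%.

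**Handling of PET results.** PET/CT is read for malignancy blind to the other results and then withheld for a year. However, section 3.4.1 provides that "findings requiring further diagnostic tests or intervention will be relayed to the chief physicians responsible for inclusion".

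**Specificity of the tracer.** The Introduction states that FDG is not specific for cancer, because inflammatory lesions also take it up.

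**The concern.** Relative accuracy has two sides: how many patients with the disease each strategy finds, and how many without it each strategy wrongly calls positive. The stated aim needs both. The stated outcomes and test supply at most the first.

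This matters here because the cohort is recruited for suspected inflammatory disease, and the article itself says that inflammation raises FDG uptake. A whole-body scan may find more cancers than X-ray plus ultrasound and also produce more false alarms. If Study III reports a significant McNemar result under an aim worded as accuracy, readers will take it to mean that PET/CT is the more accurate strategy. The comparison cannot show that.

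**Working it through.** **1. The plan's own figure.** Inputs from section 3.12: one-sided alpha 0.05 (z = 1.645), power 80% (z = 0.842), PET-only proportion 0.15, X-ray/ultrasound-only proportion 0. The total discordance and the difference are therefore both 0.15.

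n = [1.645 × √0.15 + 0.842 × √(0.15 − 0.15²)]² / 0.15² = 39.1, so 40 patients.

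The exact test needs 44. At n = 80, power is 97.6% (asymptotic) or 99.5% (exact). The claim that 80 is sufficient therefore holds on its own assumptions. The difficulty is what the test measures.

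**2. What the test measures under each reading of *detected*.**

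| Reading | What McNemar compares | What it leaves out |
|---|---|---|
| Confirmed cancer | Relative yield, equivalent to paired sensitivity | False positives do not enter |
| Positive reading | Positive calls, true and false together | False positives count in favour of the strategy with more calls |

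*Confirmed reading, hypothetical example.* Suppose there are 5 cancers in 80 patients, all found by PET/CT only. The one-sided exact P is 0.5⁵ = 0.031. It stays 0.031 whether PET/CT wrongly flags none of the other 75 patients or 20 of them, although its specificity would be 100% in the first case and 55/75 = 73% in the second.

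*Positive-reading case, hypothetical example.* Suppose PET/CT adds no true cancers and all discordance is PET-only false positives. The probability of at least 5 such calls in 80, which is one-sided significance with none the other way, is:

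| Assumed PET-only false-positive rate | None by X-ray/ultrasound only | 2% by X-ray/ultrasound only |
|---|---|---|
| 5% | 37% | 12% |
| 10% | 91% | 56% |
| 15% | 99.5% | 88% |

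These rates are assumptions; the article gives none.

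**3. How many cancers to expect.** Section 3.4.3 cites cancer in 19.5% of controls and 23.2% of PMR patients over a median of 7.8 years, a hazard ratio of 1.69 in the first 6 months, and a standardized incidence ratio of 2.26 in the first year. Assuming a constant hazard:

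- Controls: −ln(1 − 0.195)/7.8 = 0.0278 per year; 80 × (1 − e^−0.0278) = 2.2 cancers.
- PMR patients: −ln(1 − 0.232)/7.8 = 0.0338 per year; 2.7 cancers.
- Control rate with 1.69 for half a year and 1 for the rest: 0.0278 × 1.345 = 0.0374; 2.9 cancers.
- Control rate with 2.26 for the full year: 0.0278 × 2.26 = 0.0628; 4.9 cancers.

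The range is about 2 to 5. The planning assumption of 15% means 0.15 × 80 = 12 PET-only cases, more than twice the top of that range.

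**4. What 2 to 5 cancers can support.** With none the other way, exact McNemar needs 5 PET-only detections one-sided (0.5⁵ = 0.031) or 6 two-sided (2 × 0.5⁶ = 0.031). A test of sensitivity is therefore out of reach in most of this range. Even perfect sensitivity would be imprecise: the exact two-sided 95% lower limit is 0.025^(1/5) = 48% for 5 of 5, and 0.025^(1/2) = 16% for 2 of 2.

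**The case against.** **The natural reading is confirmed cancer.** The Study III title, secondary objective 2, the outcomes and the sample-size text all count malignancies, and a false-positive lesion is not a malignancy. A reader might infer from the mismatch that PET/CT can be declared better on false positives alone. The article does not support that as a general statement. It holds only on the positive-reading interpretation, which is left open mainly because section 3.4.3 compares findings with results. This limits the concern but does not remove it, because on the confirmed reading specificity is still not compared.

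**Descriptive statistics are also planned.** False-positive counts and sensitivity could be reported under that heading, so it would be wrong to say that they will never appear. The article does not commit to them, however, and the only formal comparison is on detection.

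**An article may leave the reference standard and positivity rule to the full protocol.** That is fair, and their absence is not the point made here. The point is that the aim as stated and the comparison as stated do not match.

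**McNemar suits the outcomes, and the study is exploratory.** Both are true. A paired test on confirmed detections is a sound measure of relative yield. The exploratory label does not cover the word accuracy, and section 3.12 still sets a significance threshold and claims power.

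**The expected cancer count is rough.** It combines a Swedish ratio with a UK control rate and uses incidence after diagnosis, while a screening scan may find cancers that would surface later. It should be read as an order of magnitude.

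**Conclusion.** The point stands as a mismatch between aim and analysis. Study III says that it will establish relative diagnostic accuracy for malignant and infectious diseases. Its only comparative test concerns malignancies detected. Whichever way *detected* is read, specificity is not compared and infection has no outcome, so a significant result would support a claim about yield at most.

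This conclusion rests on the wording alone and needs no assumed rate. The figure of about 2 to 5 cancers assumes a constant hazard and that the cited ratios apply to this cohort. It bears only on how far sensitivity can be tested. The false-positive probabilities are illustrations under assumed rates and apply only if *detected* means a positive reading.

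A reader might also infer that 80 patients is the wrong number. That is not supported: on the stated inputs 80 is more than enough.

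**What to change.** 1. Count as detected only malignancies confirmed by the end of the one-year follow-up, and classify each strategy's baseline reading as positive or negative against that status.
2. Keep the McNemar test on confirmed detections and present it as relative diagnostic yield.
3. Among patients without malignancy, report the paired difference in false-positive rate with a 95% CI.
4. Give each strategy's sensitivity descriptively with an exact CI, without a test.
5. State as a limitation that confirmation depends partly on PET/CT, because findings relayed to clinicians prompt the further tests that confirm cancer.
6. Replace accuracy with diagnostic yield in the abstract and section 3.4.3 if cancers are too few.
7. Add an infection outcome, or remove infection from the aim.

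**Cost.** This is mostly wording, since both baseline readings are already among the data listed in section 3.11. Final malignancy status is not in that list and must be recorded as a data field if it is not already. The sensitivity intervals will be wide, and PET/CT's advantage may look smaller once false positives stand beside detections.
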